**Methods:**

Using the ADAPT-ITT (assessment, decision, adaptation, production, topical experts, integration, training, testing) framework, we adapted the evidence-based Mentor Mother (MM) model, originally aimed at reducing vertical HIV transmission among mothers with HIV. Our mixed methods design includes (1) qualitative research, including in-depth interviews (IDIs) and focus group discussions (FGDs), to assess drivers of perinatal alcohol use and HIV risk; (2) intervention adaptation through community-based participatory workshops with stakeholders to refine the MM+ intervention in order to include culturally and contextually strategies; and (3) a pilot RCT with 100 pregnant women (≥16 years old, reporting recent alcohol use) randomized in a 1:1 ratio to the MM+ intervention (motivational interviewing [MI], including HIV and alcohol reduction messaging) or enhanced standard of care (SOC). Primary RCT outcomes include reduced alcohol use, via phosphatidylethanol (PEth) blood levels at 6-month follow-up. Secondary outcomes include uptake and adherence to pre-exposure prophylaxis (PrEP) and antiretroviral therapy (ART) among women with HIV, as well as intervention fidelity, feasibility, and acceptability.

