## Introduction

### Background

South Africa bears the highest global burden of both alcohol use during pregnancy and HIV prevalence. [1-3]. These interlinked public health crises are particularly concerning for pregnant and lactating women (PLW) due to their compounded impact on maternal, fetal, and child health. In the Western Cape province in South Africa, alcohol use during pregnancy is prevalent, contributing to some of the world’s highest rates of fetal alcohol spectrum disorder (FASD), with estimates ranging from 64 to 310 per 1000 live births [4,5]. Further, breastfeeding while consuming alcohol can impair child neurodevelopment, emphasizing the need for intervention throughout the perinatal period [6].

Pregnancy and postpartum are also periods of heightened risk for HIV, with the likelihood risk of acquisition more than doubling during this time [7]. Recent formative work among pregnant women at risk of HIV in Cape Town found that pregnant women who engage in alcohol use are more likely to report having recent condomless sex and multiple sex partners [8]. Qualitative work contextualized these findings, suggesting that alcohol use, HIV risk behaviors, nonadherence to HIV treatment, and experiences of intimate partner violence (IPV) are all inextricably linked health issues [9,10]. Despite the Joint United Nations Programme on HIV/AIDS (UNAIDS) and the World Health Organization’s (WHO) 2025 targets to eliminate vertical HIV transmission (defined as <2% HIV transmission or <50 cases per 100,000 live births) [11], South Africa’s pediatric HIV incidence still exceeds 750 per 100,000 live births. This is largely driven by a 30% antenatal HIV prevalence [11]. Considering the high HIV incidence in pregnancy, access to oral and other forms of pre-exposure prophylaxis (PrEP) are essential for PLW who do not have HIV [12,13], while women with HIV must be on and adhere to antiretroviral therapy (ART) to mitigate vertical HIV transmission [14-16]. However, alcohol use interferes with HIV care engagement, delaying ART initiation, reducing adherence, and ultimately increasing the risk of vertical HIV transmission [14-17]. Given the evidence that alcohol use disrupts biomedical HIV prevention and treatment, adherence-targeted interventions are critical.

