### Study Design for the Pilot RCT (January 2026-February 2027)

We will identify and train 3-5 mentor mothers from the community. Inclusion criteria for mentor mothers include women (≥25 years old) in the community with lived experience who are either on PrEP or have HIV and are on ART and who reported reducing or stopping using alcohol during pregnancy. Mentor mothers will be trained on the adapted MM+ curriculum and MI techniques (step 7 of ADAPT-ITT). We will include 10-15 providers (midwives, nurses, and counselors) to be part of the MM+ training and support the integration of MM+ in three antenatal care (ANC) clinics. Concomitant ante- and postnatal care, including HIV testing and ART and PrEP provision, will be provided to all women regardless of study allocation.

Following training, trained study staff in three local clinics and surrounding communities will recruit and enroll 100 pregnant women who report recent (past 2 months) alcohol use to evaluate the effectiveness and feasibility of the MM+ intervention in reducing alcohol use in PLW, PrEP use in PLW without HIV, and ART adherence in PLW with HIV (step 8 of ADAPT-ITT). Participants will be randomized in a 1:1 ratio to the MM+ study arm or enhanced standard of care (SOC). SOC is focused on HIV counseling by peers, without alcohol messaging. If we are unable to identify 100 women in the three select clinics and communities, we will expand to additional communities and clinics.

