#### RCT Outcomes

The RCT primary outcome is the preliminary effectiveness (comparing the MM+ arm to the enhanced HIV attention control arm using intention-to-treat analysis) defined as a reduction in alcohol use via biomarker-confirmed self-reported and biological samples (comparing baseline to 6 months in phosphatidylethanol [PEth] blood samples).

Secondary outcomes include (1) PrEP initiation and adherence (via patient records and urine TFV testing at 6 months) and (2) ART adherence (via urine TFV testing and self-report). In addition, we will evaluate three of the eight implementation outcomes, as defined by Proctor et al [46]: feasibility, acceptability (including participant satisfaction with the intervention), and fidelity. We will also track any social or health harms in the study and relatedness to the study intervention through study surveys and review of medical records. Table 2 describes how these outcomes will be measured. We will track session attendance, as well as ART and PrEP adherence, at each study visit.

**Table 2 table2:** Description of aim 3 implementation outcomes.

Evaluation parameter	Description	Methods	Frequency
Theoretical model	Evaluate changes in alcohol use and HIV prevention or treatment (eg, PrEP^a^ and ART^b^ use) using the theory-of-change model measuring change and which sociodemographic and behavioral characteristics are associated with change in order to understand any subpopulations receptive toward the strategic priorities and pathways of change identified by our model.	Quantitative surveys at each visit and biomarker data	Baseline and 6-month follow-up
Participants’ self-reported fidelity	Evaluate completeness of the intervention through a checklist assessing whether specific topics were covered during intervention sessions, including an assessment of the quality of intervention interactions, where participants will rate implementer engagement during intervention sessions.	Quantitative surveys at each visit and biomarker data	Baseline and 6-month follow-up

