#### Outcome Data Ascertainment

Participants will be followed for 6 months. During this time, they will have three study visits, in which they will self-report alcohol use and PrEP or ART initiation or continuation to study staff. At each study visit, we will ascertain dried blood spots for assessment of recent alcohol use, via PEth testing (PEth<20 ng/mL represents light or no consumption [47]) and AUDIT-C, a validated survey of alcohol use (0=abstinence, >0=recent alcohol use). Participant medical files will be reviewed at the end of the study to ascertain birth outcomes (including any pregnancy loss or stillbirth), reported harms, and PrEP and ART prescription. At each study visit, participants will provide a urine sample to the study staff for analysis of recent PrEP or ART use using urine TFV testing (of recent adherence in the past 72 hours). Urine TFV results will show recent adherence and will be evaluated in conjunction with viral loads (VLs). For those on ART, we will review their files for VLs to evaluate VL suppression at baseline and end of the trial (VL<200 copies/mL). If VLs are unavailable, we will track them online with the national health laboratory service.

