#### Descriptive Analysis and Effectiveness Outcomes

We will use basic measures (proportions, means and SDs, medians and IQRs, as appropriate) and graphical displays to describe distributions of key variables. Bivariable analyses will use Student's *t* tests (replaced by Mann-Whitney U tests for nonnormal distributions) or chi-square tests (replaced by exact tests for sparse data), as appropriate. We will compare study arms’ descriptive statistics without tests of statistical significance. Comparisons of randomized groups’ primary analyses will be by intention to treat, with secondary analyses based on intervention uptake. Specifically, we will evaluate reductions in alcohol use from baseline to 6-month follow-up in PEth levels, with confirmation of self-reported AUDIT-C scores compared by study arm. For secondary HIV outcomes, we will evaluate ART and PrEP adherence by study arm using urine TFV levels for recent adherence and VLs at 6 months for women on ART.

All statistical tests will be two-sided at α=.05; all effect estimates will be reported with 95% CIs. For both aims, we propose a priori subgroup analyses by age and HIV status. For subgroup analyses, effect modification will be assessed from the fully adjusted model on the additive scale by calculating the relative excess risk due to interaction [54] and on the multiplicative scale by examining the interaction term in regression models. Data will be analyzed in Stata version 15.

We will track missing variables in our monthly quality control and follow-up on all missing exposures and outcomes at each visit. We will conduct sensitivity analyses, including multiple imputation, to include evaluation outcomes and exposures from missing data and incomplete retention. Our retention efforts will focus on retention in both groups to ensure that there is no differential loss to follow-up. Analysis of implementation outcomes will entail descriptive summarization of acceptability, feasibility, and fidelity of MM+, including for women of different socioeconomic statuses or education levels.

Data management procedures will be developed with the statistical analysis plan and available upon demand to study investigators.

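### The 6-month viral-load comparison is limited to women on ART, and the plan does not fix that status at baseline

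*Protocol article*

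**What the plan says.** Under Descriptive Analysis and Effectiveness Outcomes, the Protocol article evaluates the secondary HIV outcomes by study arm "using urine TFV levels for recent adherence and VLs at 6 months for women on ART". Outcome Data Ascertainment applies the same limit to data collection: "For those on ART, we will review their files for VLs to evaluate VL suppression at baseline and end of the trial (VL<200 copies/mL". Neither section gives the time at which a woman counts as on ART.

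Other sections use a wider population. The Methods paragraph of the abstract lists "uptake and adherence to pre-exposure prophylaxis (PrEP) and antiretroviral therapy (ART) among women with HIV" as secondary outcomes. Study Design for the Pilot RCT speaks of "ART adherence in PLW with HIV (step 8 of ADAPT-ITT".

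ART uptake is also a target of the trial. The theory-of-change section names it as an intermediate outcome. Enhanced Standard of Care says that the primary aim includes learning whether the alcohol component improves adoption of ART and PrEP. The Background describes alcohol as "delaying ART initiation, reducing adherence, and ultimately increasing the risk of vertical HIV transmission".

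**The concern.** Among women with HIV, being on ART at 6 months may itself result from allocation. If MM+ brings or keeps more women on ART than control does, the two on-ART groups are no longer comparable: the MM+ group also contains women who under control would have been off ART. If those women are less often suppressed, they lower the MM+ percentage, while their counterparts in control drop out of the denominator. A real gain in suppression across women with HIV could then appear as no difference or as harm.

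The pilot is meant to inform scale-up, so a misleading viral-load contrast would matter even though it is not the primary outcome. The limit also applies to the file review, so viral loads for women off ART may never be collected.

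**Working it through.** The article gives no ART-uptake rate, suppression rate or power for this outcome, so there is no stated figure to reproduce. The check has two parts.

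**1. When is on-ART status judged?**
- *During follow-up or at 6 months.* The phrase in the analysis section sits next to the 6-month time point. Outcome Data Ascertainment has women report ART initiation or continuation at study visits, and has files reviewed for ART prescription at the end of the study. On this reading the subset is defined after randomisation.
- *At baseline.* The same section looks up viral load at baseline as well, which fits a group fixed at entry. On this reading the subset is protected by randomisation, but women with HIV who start ART during the trial never enter the viral-load comparison, so it misses any effect through uptake.

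Nothing in the article settles the choice.

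**2. Size of the possible bias under the post-randomisation reading**

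All rates are assumptions. Let b be the share of women with HIV who are on ART in either arm, d the extra share on ART only under MM+, s_a suppression among the former (the same in both arms), and s_i suppression among the extra women. Suppression off ART is set to 0.

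- On-ART contrast = (b·s_a + d·s_i)/(b + d) − s_a = d(s_i − s_a)/(b + d)
- Contrast over all women with HIV = (b·s_a + d·s_i) − b·s_a = d·s_i

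With b = 0.70, d = 0.20, s_a = 0.90, s_i = 0.50:
- On ART: (0.63 + 0.10)/0.90 = 81.1% versus 90.0%, or -8.9 points.
- All women with HIV: 73.0% versus 63.0%, or +10.0 points.

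Range, with s_a = 0.90 and s_i = 0.3, 0.5 or 0.7, for b = 0.70 (d = 0.10, 0.20), b = 0.80 (d = 0.05, 0.10, 0.15) and b = 0.90 (d = 0.05, 0.08):
- On-ART contrast: -1.1 to -13.3 points.
- All women with HIV: +1.5 to +14.0 points.

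If MM+ also raises suppression by 5 points among the women on ART in either arm, the main example gives (0.70 × 0.95 + 0.10)/0.90 − 0.90 = -5.0 points on ART, and 0.765 − 0.63 = +13.5 points overall.

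Where the reversal disappears: with d = 0, or with s_i = s_a, the on-ART contrast is exactly 0.

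**In counts.** The Background gives an antenatal HIV prevalence of 30%. Carried over to 50 women per arm (an assumption), that is 0.30 × 50 = 15 women with HIV per arm. Suppose control has 11 on ART and 10 suppressed, and MM+ has 14 on ART and 12 suppressed:
- On ART: 12/14 = 85.7% versus 10/11 = 90.9%, or -5.2 points.
- All women with HIV: 12/15 = 80.0% versus 10/15 = 66.7%, or +13.3 points.

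The second contrast is a difference of two women, and the example needs an uptake gap of 3/15 = 20 points.

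**The case against.** The strongest reply is that on ART may mean on ART at baseline, in which case there is no selection bias. That reading is open and cannot be excluded. It still leaves the viral-load population narrower than the women with HIV named elsewhere, so the text needs correcting either way. On ART could also mean prescribed ART; women who have stopped taking it but still hold a prescription would then stay in, so it cannot be said flatly that women who stop are dropped.

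Second, a large uptake gap is not obviously likely. ART provision, enhanced HIV counselling and urine tenofovir feedback are planned for both arms, and control women receive adherence counselling from mentor mothers. This stands: it makes a large bias less likely. It does not exclude one, because better ART adoption is part of what the trial sets out to study.

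Third, denominators are often left to the analysis plan, which is not shown. Here, however, the article states a denominator and applies it to data collection, so this is not an omission.

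Three stronger readings are tempting but unsupported:
- *That ART adherence and urine tenofovir are restricted too.* The limit attaches most naturally to the 6-month viral loads. RCT Outcomes defines "ART adherence (via urine TFV testing and self-report" with no such limit, and urine is collected from participants at each visit.
- *That PrEP adherence is assessed only among initiators.* No section says so; RCT Outcomes lists "PrEP initiation and adherence (via patient records and urine TFV testing at 6 months".
- *That the rule breaks an intention-to-treat promise.* That commitment is made for the primary analyses, and the HIV outcomes are secondary.

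**Conclusion.** The point holds for viral load only. The article fixes an on-ART denominator without a time point, while ART uptake is a target of the intervention and the ART outcome is elsewhere given for women with HIV. Judged after randomisation, the comparison can be biased, by roughly 1 to 13 points in the wrong direction over the assumed rates. Judged at baseline, it is unbiased but incomplete.

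A reader might infer that the viral-load result will come out reversed. The documents do not support that. Reversal needs status judged after randomisation, more women on ART under MM+, and poorer suppression among those extra women, and the article gives no rate for any of these. The outcome is secondary, in a pilot with about 15 women with HIV per arm if the 30% prevalence carries over. The correction is worth making because it is cheap and removes the possible bias.

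**What to change.** - Define the viral-load population as all randomised women with HIV at baseline, analysed in their allocated arm.
- Look up viral loads for all of them, using the file review and national laboratory search already planned.
- Count a woman who is not on ART at 6 months and has no suppressed viral load (under the article's limit of 200 copies/mL) as not suppressed. Use multiple imputation only for values that are truly missing.
- Report the result among women on ART as descriptive, and state when that status is judged.
- Reconcile the abstract, Study Design for the Pilot RCT, Outcome Data Ascertainment, and Descriptive Analysis and Effectiveness Outcomes, so that all four name the same population.

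The cost is a sentence or two of analysis wording, a slightly wider record review, and somewhat lower suppression percentages, since women off ART enter the denominator. The number enrolled and the study visits do not change.

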#### Mixed Methods Analyses

We will conduct an explanatory sequential mixed methods design [55], collecting and analyzing quantitative data first (surveys, monitoring forms), followed by qualitative interviews with a purposively selected subsample of health care providers and participants to expand on findings from the quantitative phase.

### Ethical Considerations

We have obtained approval from relevant institutional review boards (University of California, Los Angeles [UCLA] IRB#24-0130, HSRC REC #2/31/01/24). Prior notice will be given, and informed consent will be sought and obtained from all study participants. All participants will go through an informed consent process. The study staff will provide information for those who are interested in being tested but not interested in study participation. All study participation is strictly voluntary, and participants can refuse specific procedures or further study participation at any time.

Study staff members who will have contact with participants will receive training on the protection of human subject research before engaging in study-related activities. Additionally, the staff will undergo Good Clinical Practices (GCP) training, as required. Evidence of ethics training will be submitted with every ethics approval application and maintained throughout the study.

All potential participants will read the informed consent form (ICF) or have the ICF read to them. The ICF will be available in relevant local languages (eg, Afrikaans, isiXhosa) and English, and participants will complete the informed consent process in their preferred language. Each participant will be given an opportunity to ask questions about study participation. If a participant agrees to participate in the study, the study staff will obtain written consent. After consenting to participate, the participant may voluntarily withdraw from the study at any time and can choose not to have their responses submitted to the study team. Study participation is voluntary, and we will ensure ongoing respect of participants throughout the research process through ensuring confidentiality and privacy principles.

To ensure confidentiality, all data will be coded by participant number. Data recorded on paper will be kept in locked cabinets with access only to members of the research team. There will be strict limited access to electronically stored data, using password protection. Research records will be kept confidential following national regulations. Every participant’s name or other personal identifiers will not be included with specimens sent to the laboratory, which will be identified only by a code number. Interviewers and support staff will be trained on procedures for maintaining confidentiality.

We will use phone calls and text messages for follow-up to improve retention. Text messages will be neutral and not contain personal information about the participants (eg, appointment reminders will say, “Your appointment is on Tuesday at 3:00 p.m.”). At each visit, staff will ask about social harms, complete a detailed report, link the participants to community resources for support, and report social harms to the ethics review board. If multiple social harms are observed, the study procedures and text message content will be reviewed by the study team and CABs and recommended changes submitted to regulatory bodies for review.

All data collection procedures, regardless of the source, will follow standardized procedures outlined in the *Manual of Operating Procedures*, with individual activities guided by SOPs. RCT data (aim 3) will be collected by trained study interviewers using REDCap electronic software, which is Health Insurance Portability and Accountability Act (HIPAA)– and Protection of Personal Information Act (POPIA)–compliant for research studies. The interviewers will ask questions and complete the responses using a handheld tablet with internet connectivity for rapid data access and quality control.

The Data Safety and Monitoring Board (DSMB), which will comprise experts in the field of HIV and substance use in pregnancy, will be formed in the first year of the study and will meet quarterly to evaluate safety outcomes and data monitoring. A CAB was formed in 2025 that includes pregnant individuals, health care providers, and community leaders from Saldanha Bay and has held two meetings to date. CAB members are supporting the study by providing input, guidance, and feedback on the study’s methodology and implementation throughout the study period, ensuring community perspectives are considered.

## Results

We launched our formative work in January 2025 with community research in Saldanha Bay. We conducted 2 FGDs with health workers (n=6) and community leaders (n=7), as well as 31 IDIs with partners and peers of PLW who reported alcohol use during pregnancy. We have conducted the initial rapid analysis of the results. Participants reported that PLW have strong motivations to reduce alcohol use for their child’s health but face multiple barriers, including misconceptions about the safety of alcohol in pregnancy, poverty, trauma, IPV, social pressure to drink to connect with peers, and stigma. Alcohol use was frequently linked to financial stress (particularly around the need to support a child), an unplanned pregnancy, and poor mental health. Preferred support strategies emphasized nonjudgmental, peer-based mentorship, family and partner engagement, and involvement of faith and community networks and leaders. Additional gaps included stigma surrounding HIV prevention (PrEP awareness, access, and use were limited) and contraceptive services. Communities recommended that mentor mothers be women with lived experience who are empathetic, discreet, and culturally relatable, with structured training, supervision, and referral linkages.

Following rapid analysis, a community workshop was convened in August 2025 with 29 stakeholders, including community leaders, health professionals, social workers, and people with lived experience, to refine the MM+ intervention. Participants reinforced the importance of mentor mothers as trusted, trained women with lived experience, and highlighted priorities, such as clear, culturally relevant education on alcohol use, HIV prevention, and family planning; trauma and IPV support; and flexible delivery across home, community, and group settings.

The next steps include identification and training of mentor mothers, finalization of intervention materials, and preparation for implementation of the RCT.

